## **2 Statistical considerations**

### **2.1 Definition of analysis populations**

#### **2.1.1 PDAC population**

The PDAC population will consist of 25 participants with a known diagnosis of PDAC.

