#### **2.5.1 Model building**

Logistic regression models will be constructed predicting PDAC status using  $^{13}\text{C}$ -mixed triglyceride breath test and faecal elastase values as described in section 2.4. Multivariable logistic regression models will then be constructed with the aim of finding the best-fitting combination of cut-offs for the  $^{13}\text{C}$  and faecal elastase values.

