#### **3.3 Primary endpoint**

##### **3.3.1 Pancreatic cancer diagnosis**

The primary endpoint for this study is the prediction of PDAC. PDAC status is known at recruitment (i.e. all participants in the PDAC cohort are positive, all others are negative). Several logistic multivariable models will be constructed using results from the C-mixed triglyceride breath test and fecal elastase tests, with appropriate data transformations as outlined in section 2.4. All final regression model results will be reported. Models will be validated and adjusted for optimism using bootstrapping techniques (Steyerberg *et al*, 2001). Performance measures include sensitivity, specificity, positive predictive value, and negative predictive value. In order to evaluate these, numerous cut-offs for defining predicted cancer positivity in the underlying risk score will be evaluated with the study team. Discrimination will be measured using the R2 and D statistic. Calibration will be assessed visually with the aid of calibration plots, comparing observed and predicted risks in each tenth of predicted risk.

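### SAP section 3.3.1 names R2 and the D statistic as discrimination measures for logistic models and gives no suitable threshold-free measure; calibration by tenths would rest on 5 to 6 people per group

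*SAP*

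**What the plan says.** SAP section 3.3.1 sets out the primary analysis. The outcome is binary and has no time element: "PDAC status is known at recruitment (i.e. all participants in the PDAC cohort are positive, all others are negative". The models are logistic: "Several logistic multivariable models will be constructed using results from the" breath test and the faecal elastase test.

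The same section then lists how performance will be judged:

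- Accuracy at thresholds: "Performance measures include sensitivity, specificity, positive predictive value, and negative predictive value", at a range of risk-score cut-offs to be looked at with the study team.
- Discrimination: "Discrimination will be measured using the R2 and D statistic".
- Calibration: by eye from plots "comparing observed and predicted risks in each tenth of predicted risk".
- Internal validation: "Models will be validated and adjusted for optimism using bootstrapping techniques".

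Section 2.5.1 adds the modelling aim: "Multivariable logistic regression models will then be constructed with the aim of finding the best-fitting combination of cut-offs for the" two tests. Section 2.4.1 uses the Youden index to choose a breath-test cut-off at each time point. Section 2.4.2 allows faecal elastase to enter either as cut-offs or as a continuous value.

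On numbers, section 2.1.1 says: "The PDAC population will consist of 25 participants with a known diagnosis of PDAC". Sections 2.1.2 and 2.1.3 add 25 healthy controls and at most 10 people with chronic pancreatitis, so N is 50 to 60. No c-statistic, ROC curve or AUC is named anywhere in the SAP, and no calibration slope or intercept.

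**The concern.** Both objectives in SAP section 1.4 are discrimination questions: whether the tests separate PDAC from healthy volunteers, and whether the shorter breath tests classify as well as the 4-hour test. The sentence that assigns the discrimination measures names two that do not suit the model.

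D describes prognostic separation in survival models. There are no survival times here, and the SAP does not say how D would be computed for a logistic model. R2 describes overall fit. It combines calibration with discrimination, has several variants for binary outcomes that give different numbers, and changes with the proportion of cases. The design chooses that proportion, so it tells the reader nothing about clinical practice.

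The gap matters most for Objective 2. Each time point has its own breath-test cut-off, so a comparison of time points through sensitivity and specificity mixes the quality of the test with the choice of cut-off. A threshold-free summary avoids this. Leaving the R2 variant and the form of D open also invites a choice after the data are seen, which section 1.1 says the SAP is meant to prevent.

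The calibration display has a separate problem: too few people per group to read and, for some of the planned models, too few distinct predicted risks to form the groups.

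**Working it through.** **Inputs.** 25 PDAC, 25 healthy and 0 to 10 chronic pancreatitis participants (sections 2.1.1 to 2.1.3). Planning difference 17.8%, SD 10.5%, two-sided 5% (section 1.8). Section 1.8 gives the SD for the cancer group only; I assume that it applies to both groups and that values are normal.

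**1. The plan's own figure.** Section 1.8 states 100% power. 17.8 / (10.5 × √(2/25)) = 5.99, and power = Φ(5.99 − 1.96) = 0.99997. It reproduces. It is used below only as the source of a plausible effect size.

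**2. Is an AUC estimable?** Separation d = 17.8/10.5 = 1.695. AUC = Φ(d/√2) = Φ(1.199) = 0.885.

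Hanley-McNeil standard error with A = 0.885: A/(2 − A) = 0.793, 2A²/(1 + A) = 0.831, A² = 0.783. For 25 v 25, carrying full precision, SE = √{[A(1 − A) + 24(0.793 − 0.783) + 24(0.831 − 0.783)]/625} = √[(0.102 + 0.253 + 1.149)/625] = 0.049. The half-width is 1.96 × 0.049 ≈ 0.10. If the true AUC were lower, the 25 v 25 intervals would be about 0.55 to 0.85 (AUC 0.70) and 0.68 to 0.92 (AUC 0.80).

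**3. Does R2 depend on the case fraction?** Hold d = 1.695, so AUC stays at 0.885, and change only the case fraction π. The true risk is p(x) = expit[logit π + dx − d²/2]. With L and L0 the expected log-likelihoods per person of this model and the null model:

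- Cox-Snell = 1 − exp[2(L0 − L)]
- Nagelkerke = Cox-Snell / [1 − exp(2·L0)]
- Tjur = mean p in cases − mean p in non-cases

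| Case fraction | AUC | Nagelkerke | Tjur |
|---|---|---|---|
| 25/50 | 0.885 | 0.55 | 0.45 |
| 10% | 0.885 | 0.41 | 0.31 |
| 1% | 0.885 | 0.26 | 0.09 |

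At 25/60 the values are almost the same as at 25/50 (Nagelkerke 0.547 against 0.551). The dependence is therefore small within the study's own range and large once the result is carried to a lower case fraction. The variants also differ at a single fraction: at 25/50 Cox-Snell is 0.41, Tjur 0.45 and Nagelkerke 0.55.

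**4. Does R2 isolate discrimination?** In a simulated data set of 25 cases and 35 non-cases, a fitted logistic model had AUC 0.866 and Nagelkerke R2 0.46. Multiplying the linear predictor by 3 gave R2 −0.04; adding 2 to it gave −0.28. The ranking, and so the AUC, stayed at 0.866 throughout. R2 reacted to miscalibration alone.

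**5. Calibration by tenths.** 50/10 = 5 and 60/10 = 6 people per tenth, so the observed risk moves in steps of 0.20 or 0.17. Wilson 95% interval for 3/5, with z² = 3.84: centre (0.6 + 3.84/10)/(1 + 3.84/5) = 0.557; half-width 1.96 × √(0.24/5 + 3.84/100)/1.768 = 0.326; interval 23% to 88%. The exact interval is 15% to 95%. Fifths (10 to 12 people) do not solve it: 5/10 has an exact interval of 19% to 81%.

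**6. Distinct predicted risks.** One breath-test cut-off gives 2 levels. Faecal elastase gives 2 levels with one cut-off, or 3 with both. 2 × 2 = 4 and 2 × 3 = 6, fewer than the ten groups required.

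**The case against.** The strongest reply is that the SAP already covers discrimination. Section 3.3.1 plans sensitivity and specificity at several cut-offs of the risk score, which are points on a ROC curve, and plans bootstrap optimism adjustment of the models. Section 2.4.1 adds the Youden index. Section 3.4 reports the distributions of both tests by cohort. This stands. A reader might infer from the unsuitable measures that the key performance results will be missing or uninterpretable, or that nothing will be comparable with other diagnostic studies. The SAP does not support that: accuracy at thresholds is planned and is interpretable. Only the threshold-free summary is lacking.

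A second reply is that R2 and D are not wholly silent on discrimination. This also stands. Tjur's variant reflects separation, and a D-type separation could be computed on a linear predictor. It would be too strong to say that neither can carry any such information. But the SAP names no variant and no adaptation, and step 3 shows that even Tjur's version moves with the case fraction.

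A third reply is that tenths can be formed when continuous values enter the model, as section 2.4.2 allows. That is correct; the impossibility is confined to models made only of binary cut-offs. Tenths from continuous models would still hold 5 to 6 people. A gross pattern across the plot might still show, so it would be too strong to say that the plot could detect nothing. Much of the imprecision comes from N = 50 to 60 and would affect a smoothed curve too.

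**Conclusion.** The point holds as a fault of choice and definition in section 3.3.1. The named discrimination measures are unsuited to a logistic model of a status known at recruitment and are left undefined. The SAP therefore has no suitable threshold-free measure with which to answer Objective 1 or to compare the 1, 2 and 3-hour tests with the 4-hour test. Discrimination at chosen thresholds will still be reported, and nothing here shows that the planned outputs would lead to a wrong conclusion.

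On size: with separation held constant, Nagelkerke R2 falls from 0.55 to 0.26 as the case fraction goes from 50% to 1%, while the AUC stays at 0.885. An AUC of that order could be estimated to about ±0.10 with 25 v 25. These figures assume normality and a common SD of 10.5%. The calibration weakness, 5 to 6 people per tenth, follows directly from the planned numbers. It is a matter of precision and presentation, and for models built only from cut-offs one of feasibility, given one breath-test cut-off per model.

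This should be fixed before the analysis. Because threshold-based accuracy is already planned, it does not rank as a defect that undermines the study.

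**What to change.** In SAP section 3.3.1:

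- Replace the discrimination sentence with: *Discrimination will be measured by the c-statistic (ROC AUC) with 95% CI, apparent and bootstrap optimism-corrected.*
- Delete the D statistic.
- Keep R2, with the variant named, or the Brier score, as a measure of overall performance only.
- Replace calibration by tenths with the bootstrap optimism-corrected calibration slope and, for models with continuous predictors, a smoothed calibration curve.
- State that absolute predicted risk reflects the case-control sampling ratio, and that calibration will remain imprecise at N = 50 to 60.

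The cost is SAP wording only. No new data are needed, and the output is standard in Stata or SAS, the packages named in section 2.2.

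### Calibration is judged only by eye, in tenths of 5 to 6 people, with no calibration statistic and no statement that the bootstrap optimism correction covers it

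*SAP*

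**What the plan says.** All the relevant wording on assessment is in SAP section 3.3.1.

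- Models: "Several logistic multivariable models will be constructed using results from the" breath test and the faecal elastase (FE-1) test. No penalised method is mentioned.
- Validation: "Models will be validated and adjusted for optimism using bootstrapping techniques". The number of resamples, the quantities to be corrected and the steps to be repeated in each resample are not given.
- Accuracy: "Performance measures include sensitivity, specificity, positive predictive value, and negative predictive value".
- Discrimination: "Discrimination will be measured using the R2 and D statistic".
- Calibration: "Calibration will be assessed visually with the aid of calibration plots", which set observed against predicted risk by tenths of the predictions.
- Reporting: "All final regression model results will be reported". Nothing is said on whether the reported coefficients are shrunken.

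Section 2.5.1 adds that the multivariable models are built "with the aim of finding the best-fitting combination of cut-offs for the" breath-test and FE-1 values, so part of the model is chosen from the data. Sections 2.1.1 to 2.1.3 set 25 PDAC cases, 25 healthy controls and up to 10 people with chronic pancreatitis. Section 3.3.1 counts everyone outside the PDAC cohort as negative. No separate validation cohort is described.

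**The concern.** Accuracy and discrimination each have a named number that a bootstrap can correct. Calibration has only a picture, and the SAP leaves open which predictions go into it. An analyst could follow the text to the letter, plot the apparent predictions and describe the calibration. Such a plot may expose a wrong functional form. It cannot show that predicted risks are too spread out, which is the typical result of fitting and searching in a sample with 25 cases.

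At stake is what the report can say about the reliability of its risk scores within the recruited mix of cases and controls. Section 1.1 states that the SAP is meant to prevent decisions made after the data are seen, and this choice is left to that stage.

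**Working it through.** **1. The SAP's own design figure.** Section 1.8 gives 25 per group, a difference of 17.8%, an SD of 10.5% (stated for patients; taken here as common to both groups), two-sided 5%, and 100% power.

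- 17.8 / (10.5 × √(2/25)) = 17.8 / 2.970 = 5.99.
- Power = Φ(5.99 − 1.96) = 99.997%; with the noncentral t, 99.995%.

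The stated 100% reproduces. It does not bear on calibration, for which the SAP gives no figure. It does supply one effect size: 17.8 / 10.5 = 1.70 SD.

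**2. Why an apparent plot cannot show over-fitting.** An unpenalised maximum-likelihood logistic fit with an intercept satisfies Σ(y − p) = 0 and Σxⱼ(y − p) = 0 for every predictor. The linear predictor LP is a linear combination of these terms, so ΣLP(y − p) = 0. Now refit logit P(y = 1) = a + b·LP in the same data. Its score equations are already solved at a = 0, b = 1, and without separation that solution is unique. The apparent slope is therefore 1 whatever the degree of over-fitting. With coefficients pooled over imputed data sets (section 2.3.2) this holds only approximately.

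**3. How much a plot by tenths can show.** 50 / 10 = 5 and 60 / 10 = 6 people per tenth. The exact 95% interval for 3 of 6 is 12% to 88%, and for 2 of 5 it is 5% to 85%. Even corrected predictions would be hard to judge at that resolution.

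**4. Slope in new data with the same case mix, by number of predictors.** Simulation with 25 cases and 35 non-cases. Assumptions not in the SAP: two informative predictors shifted by 0.8 or 1.2 SD, predictor correlation 0.5, no selection; 100 data sets per setting and 60 resamples each.

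| Predictors | Apparent slope | Bootstrap-corrected, median | New data, median |
|---|---|---|---|
| 2 | 1.0000 | 0.92–0.93 | 0.84–0.95 |
| 3 | 1.0000 | 0.84–0.85 | 0.75–0.82 |
| 5 | 1.0000 | 0.72–0.75 | 0.67–0.73 |
| 8 | 1.0000 | 0.58–0.63 | 0.52–0.59 |

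Fits that did not converge were left out (2 and 16 of 100 in the two settings with 8 predictors). The corrected slope moves in the right direction but was up to 0.09 too favourable (0.93 against 0.84 with 2 predictors).

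**5. Effect of selection.** Simulations closer to this study used eight correlated time points plus FE-1, a breath-test effect of 1.0 or 1.7 SD and an FE-1 effect half as large. Apparent slope: 1.00 throughout. Two sets of runs gave these median new-data slopes:

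- Fixed model, 4-hour value plus FE-1: 0.82–0.88 and 0.85–0.91, together 0.82–0.91.
- Best-fitting of the eight time points plus FE-1: 0.75–0.79 and 0.73–0.82, together 0.73–0.82.

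When the bootstrap repeated the selection it gave 0.76–0.77 against true medians of 0.77–0.79. Runs that added a weaker 0.7 SD effect and the 10 extra controls gave 0.82–0.93 (fixed) and 0.65–0.81 (selected). The search over cut-offs in section 2.5.1 was not simulated; it would be expected to add optimism.

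**The case against.** The strongest reply is the bootstrap sentence in section 3.3.1. It says the models themselves are adjusted for optimism, and a competent analyst could take that to include a corrected calibration curve and shrunken coefficients. A curve can be corrected without first naming a summary number. This stands in part: the SAP allows that reading but does not commit to it.

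Three stronger readings are tempting and are not supported.

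- *The plot is made from apparent predictions and the reported coefficients are too extreme.* The SAP says neither. It is silent on which predictions are plotted and on shrinkage.
- *Over-fitted risks would distort the positivity cut-offs.* Multiplying the coefficients by one positive slope and re-estimating the intercept is a monotone change of the score. Ranking is unchanged, each cut-off is simply relabelled, and sensitivity, specificity, PPV and NPV stay the same. The objectives in section 1.4 concern distinguishing and classifying, not individual absolute risk.
- *A patient told 90% should have been told less.* At slope 0.77, logit(0.90) = 2.197 becomes 1.692, or 84%, taking the calibration intercept as zero. That holds only in the recruited case mix. This is a case-control study (section 1.7), so neither figure is a real patient's risk.

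Nor would the planned plot always look good. In a two-predictor simulation the mean in-sample gap between observed and predicted risk per tenth was 10 to 14 percentage points. Its weakness is noise together with blindness to the slope.

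Selecting the best of eight time points is also an assumption: section 2.5.1 speaks of cut-offs, and section 1.4 compares the 1-, 2- and 3-hour tests with the 4-hour test.

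**Conclusion.** The point holds as a gap in specification. Calibration is visual only, in groups of 5 to 6, with no statistic, and the SAP does not say that the bootstrap correction extends to it. If apparent predictions are plotted, over-fitting cannot be seen.

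The over-fitting that could go unseen is modest for a fixed two-predictor model (median new-data slope roughly 0.82 to 0.91) and larger if the best-fitting time point is chosen (0.73 to 0.82). These ranges rest on assumed effects of 1.0 to 1.7 SD for the breath test and half of that for FE-1, and on new data with the recruited case mix. Only the 1.70 SD figure comes from the SAP.

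Classification results are not affected by this point. It is worth changing because the remedy is nearly free inside a bootstrap already planned.

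**What to change.** In section 3.3.1, replace the visual check by tenths with the following:

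- For each final model, report the bootstrap optimism-corrected calibration slope, with the time-point and cut-off selection repeated in every resample.
- Replace the plot by tenths with an optimism-corrected smoothed calibration curve.
- State that calibration refers to the recruited case mix only.
- State whether the reported coefficients are shrunken. Shrinkage by the corrected slope is optional: at this size the estimated and true slopes agreed poorly within single data sets (correlation between +0.41 and −0.47), and shrinking brought the new-data slope closer to 1 in only 60 to 65% of them.

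The cost is a few lines of text and a little more code. The calibration result will probably look less favourable, and the slope will be imprecise with 25 cases, which the report should say.

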#### **3.4 Secondary endpoints**

The distribution of C cumulative exhalation will be summarised at 1, 2, 3 and 4-hours, by cohort.

The proportion of participants with C cumulative exhalation below cut-offs outlined in section 2.4.1 will be summarised by cohort.

The proportion of participants whom remain seated during the 4-hour C-mixed triglyceride breath test will be summarised by cohort.

The distribution of the faecal elastase test will be summarised by cohort, including the proportion of participants who returned a sample and whether the sample was collected at the visit or post-visit.

#### **3.5 Additional analyses**

No additional analyses will be reported.

#### **3.6 Safety reporting**

No safety measures will be reported.

#### 4 SAP revision history

| Version number | Revision history                                                                                       | Author      | Date        |
|----------------|--------------------------------------------------------------------------------------------------------|-------------|-------------|
| 0.1            | Created using template                                                                                 | [name] | 21-Apr-2021 |
| 0.2            | Incorporated changes from [name], taken sample size information from the protocol            | [name] | 23-Jul-2021 |
| 0.3            | Additional information on 13c test added by [name], and additional reference by [name] | [name] | 19-Oct-2021 |
| 1.0            | Escalated to v1.0                                                                                      | [name] | 27-Oct-2021 |
